### 5.1.4 Adherence Assessment

In this trial, the study intervention (IVF with or without PGS) will be performed by local embryologists in laboratory. Adherence is expected to be high. No special assessment is planned in this trial. From our previous experience, subjects may choose or doctors may recommend alternate forms of IVF treatment after randomization, and they will be free to do this. We will track this and anticipate it will occur infrequently ( $<5\%$  of subjects). If deviations or violations from protocol occur, they will be recorded by standard forms.

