## 8 CRITERIA FOR INTERVENTION DISCONTINUATION

*List criteria for discontinuing intervention and methods for determining when criteria are met. Include procedures for maintaining subject participation in followup activities.*

The intervention is the performance of PGS on up to 3 blastocysts. It will be discontinued at patient or physician request if the patient is assigned to the PGS group.

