## 9.2 Outcomes

### 9.2.1 Primary outcome

The primary outcome is the cumulative live birth rate over the (up to) 3 embryo transfers. Live birth is defined as the delivery of any viable infant at 28 weeks or more of gestation after our interventions, and cumulative live birth rate is calculated by dividing the number of women achieving live birth after transfers of all euploid embryos in the PGS group or 3 blastocysts in the IVF group within 1 year after randomization, by the total number of women randomized to the specific group.

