#### 9.5 Data Analyses

The primary analysis will be performed in accordance with the principle of intent-to-treat. Continuous variables will be described as mean  $\pm$  standard deviation for the normally distributed variables and as median and range for the non-normally distributed variables. Category variables will be presented as frequency and percentage. The differences in the cumulative live birth rate in the two treatment arms will be compared by absolute risk difference and its 95% confidence interval (CI). The relative risk and its 95% CI will also be calculated. Non-superiority of PGS to IVF will be considered to be established if the upper limit of the 95% CI of absolute risk difference was shown to lie below the non-superiority margin of 7%.

The differences in the secondary outcomes such as rate of Good Birth Outcome, cumulative pregnancy rate, cumulative pregnancy loss rate, multiple pregnancy rate obstetric and neonatal complications will be tested by Person chi-square analyses. The absolute difference and 95%CI as well as relative risk and 95% CI will also be calculated. The difference between duration of pregnancy, birth weight and times of embryo transfer will be tested by student t test and non-parameter test if necessary.

The tertiary outcomes such as the rates of pregnancy, pregnancy loss and live birth after the first transfer will be analyzed with Pearson chi-square test. Cost-effectiveness analysis will be done by decision analytic model with TreeAge Pro 2014 (2014 Version; TreeAge

software). Cost effectiveness is defined as an incremental cost effectiveness ratio (ICER). The ICER for live birth was calculated as the difference in cost between two treatment groups divided by the difference in live birth rates between the two groups. The secondary analysis will be performed according to per-protocol analyses. The primary and secondary outcomes will be compared according to actual treatment that subjects received and among subjects who complete embryo transfer(s).

Subgroup analyses will be performed according to different stimulation protocol (e.g. agonist long, agonist short, and antagonist protocol), different endometrial preparation protocol for FET (e.g. natural ovulation cycle and artificial cycle), age groups (e.g. 20~30 group, 30~35 group and >35 group), with or without history of recurrent spontaneous abortion.

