**Final statistical analysis**

Given the possibility of false positive and the decision of not transferring mosaic embryos which are probably to develop into live birth, we hypothesized that the cumulative live birth rate after the transfer of PGT-A-selected euploid blastocysts is not clinically better than that after serially transferring all the 3 untested blastocysts. This study was therefore designed as a non-superiority study. It was estimated the cumulative live birth rate after 3 single embryo transfers was 65% in each group. To be 80% certain that the upper limit of a one-sided 95% confidence interval (CI) would exclude a difference in favor of the PGT-A group by more than 7%, 575 patients were required in each group. In consideration of 5% drop-out rate, a total of 1,208 patients were needed.

Continuous baseline characteristics of PGT-A and IVF groups were represented as means  $\pm$  SD, and between-group differences were compared by Wilcoxon rank-sum test. Categorical variables were represented as frequencies and percentages, and compared by chi-square test. Fisher's exact test was performed for the number of frequencies less than five. Non-superiority test was used to evaluate the absolute rate differences with a two-sided 90% CI for the primary hypothesis only. Other categorical variables were analyzed by estimation of absolute rate differences and relative rates with a two-sided test. Kaplan-Meier curves were used for the time to live birth. We also conducted secondary analyses based on actual treatment that the patients received, the initial, secondary and third embryo transfer in PGT-A and IVF groups. Subgroup analyses were performed according to different endometrial preparation protocol for frozen embryo transfer and age groups. Two-sided P value of  $<0.05$  were considered significant. All analyses were performed using SAS software (version 9.4, SAS Institute).

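### The secondary analysis labelled per-protocol is described as an as-treated comparison, which is not randomised and can be biased if switching is related to prognosis

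*Combined protocol and SAP*

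**What the plan says.** Section 9.5 sets the primary analysis clearly: "The primary analysis will be performed in accordance with the principle of intent-to-treat". Section 9.2.1 agrees, since the number of women with a live birth is divided "by the total number of women randomized to the specific group".

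For the secondary analysis, Section 9.5 says: "The secondary analysis will be performed according to per-protocol analyses". The next sentence explains what is meant: "The primary and secondary outcomes will be compared according to actual treatment that subjects received". It then adds a restriction to women who complete embryo transfer. The same text stands in the statistical plan at the front of the protocol. The Final statistical analysis section no longer uses the per-protocol label but keeps the grouping: "We also conducted secondary analyses based on actual treatment that the patients received". Neither document defines a per-protocol set, says that women stay in their randomised arm for this analysis, or says how switchers are handled.

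Three other places bear on switching:

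- Assignment is made known to women and physicians (Section 4.3.4), and the trial is open-label (Section 5.2).
- Section 5.1.4 states that "subjects may choose or doctors may recommend alternate forms of IVF treatment after randomization, and they will be free to do this". It expects this in under 5% of subjects and says it will be tracked.
- Section 8 says of the intervention: "It will be discontinued at patient or physician request if the patient is assigned to the PGS group".

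**The concern.** A per-protocol analysis keeps women in their randomised arm and restricts it to those who adhered. An as-treated analysis classifies women by what they received. The plan uses the first name and describes the second.

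The difference matters because a switcher who is reclassified leaves one side of the comparison and joins the other. If switchers differ in prognosis, both rates move, in opposite directions. Since allocation is known and switching is a matter of choice or advice, randomisation does not protect this comparison.

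The design makes adherence worth a good secondary analysis. Switching pulls the intention-to-treat difference towards zero, and in a non-superiority trial that favours the claim. A reader will want to know whether non-adherence contributed to the result, and an as-treated comparison is a weak way to find out.

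**Working it through.** **Inputs from the documents.** Live-birth rate 65% (Section 9.3; the Synopsis and the Final statistical analysis section give it for each group), margin 7 points, one-sided 5% level, 80% power, 575 per group, 1208 in total, 1:1 allocation. Switching is expected in under 5% of subjects, with no direction and no prognosis given.

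**The plan's own figure.** n = (1.645 + 0.842)² × 2 × 0.65 × 0.35 / 0.07² = 6.183 × 0.455 / 0.0049 = 574.1, so 575 per group. This matches. Then 575 × 1.05 = 603.75, so 604 per arm and 1208 in total.

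**Hypothetical one-way switching.** Assume no true effect, so both randomised arms are at 65%. A share s of the PGS arm crosses to IVF and nobody crosses the other way. Switchers' live-birth rate minus stayers' rate is g.

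- Stayers' rate = 0.65 − s·g; switchers' rate = stayers' rate + g.
- As-treated PGS rate = stayers' rate.
- As-treated IVF rate = (0.65 + s × switchers' rate) / (1 + s).
- The difference reduces to −2sg / (1 + s).

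For s = 0.05 and g = −0.20, stayers are at 66.0% and switchers at 46.0%. The as-treated IVF rate is (0.65 + 0.05 × 0.46) / 1.05 = 64.1%, so the difference is +1.9 points when the truth is zero.

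| s | g | As-treated difference (points) |
|---|---|---|
| 5% | −20 / +20 points | +1.9 / −1.9 |
| 5% | −10 / +10 points | +0.95 / −0.95 |
| 2% | −20 / +20 points | +0.8 / −0.8 |
| 2% | −10 / +10 points | +0.4 / −0.4 |

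**Two-way switching.** If 5% cross each way with the same live-birth rate, each as-treated group still averages 65% and the bias is 0. If 5% cross each way with opposite prognosis (45% for those leaving PGS, 85% for those leaving IVF), the rates are 67.0% and 63.0%, a bias of +4.0. The direction and prognosis of switching therefore decide the answer, and the documents give neither.

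**Dropping switchers instead of moving them.** In the one-way case the difference is −s·g. For s = 0.05 and g = −0.20 that is 66.0 − 65.0 = +1.0 point. About half of the as-treated bias remains.

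**Complier-average effect.** This is the intention-to-treat difference divided by the difference in PGS uptake between arms. In the one-way case uptake is 0.95 against 0, and 0 / 0.95 = 0 whatever g is. The standard error of the intention-to-treat difference at 604 per arm is √(0.455 / 604) = 2.74 points. Treating the divisor as fixed, the interval widens by 1 / 0.95 = 1.053. The half-width goes from 4.51 to 4.75 points at the two-sided 90% level, or from 5.38 to 5.66 at 95%.

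**Scale of the question itself.** If the effect in compliers were 7 points, 5% one-way switching would dilute it by 0.05 × 7 = 0.35 points. In the 20-point scenario the as-treated bias of 1.9 points is about five times that.

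**The case against.** **The wording may only restrict.** The Section 9.5 sentence could mean women who received what they were allocated and completed transfer. No sentence says outright that switchers are moved across. This has some force for Section 9.5, where the analysis set is undefined. But comparing by treatment received ordinarily means grouping by it, and the Final statistical analysis section repeats that grouping without the per-protocol label. The label mismatch lies in Section 9.5 and its copy at the front; the as-treated grouping appears in all three places.

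**Direction of switching.** A reader might infer from Section 8 that switching runs mainly from PGS to IVF. The documents do not support this. Section 8 names only the PGS arm because PGS is the intervention, so only that arm has something to stop. Section 5.1.4 is neutral between arms.

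**Prognosis of switchers.** The 10- and 20-point gaps have no source. Randomisation and biopsy both fall on culture day 5, which leaves little time to decline PGS, and every randomised woman has at least three good-quality blastocysts. The sequencing result comes only after PGS has been received. All this limits prognosis-related switching but does not rule it out.

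**The 5% figure.** Section 5.1.4 counts all subjects and any alternate form of IVF treatment. It is not a ceiling on crossover within the PGS arm, and true crossover could be lower or higher.

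**Consequence.** A reader might take this analysis as the plan's formal check on the primary result, or conclude that its agreement or disagreement with intention-to-treat cannot be interpreted. Neither follows. Non-superiority rests on the intention-to-treat difference alone, and the one-way distortions above are 0.4 to 1.9 points.

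**The completer clause.** Restricting to women who complete transfer is a separate matter and may bias more. At 60% euploidy (Section 2.1) and independent embryos, 0.4³ = 6.4% of PGS women would have no euploid embryo, and 65 / 0.936 = 69.4%, or +4.4 points. That objection is fair, but it does not remove the point about grouping.

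**Conclusion.** The point holds as a defect of the secondary analysis. The label and the description in Section 9.5 disagree, and the analysis as described is not a randomised comparison. Bias is possible if switching is related to prognosis, but it is not demonstrated. Under the assumption of 5% one-way crossover from PGS with a 10- to 20-point difference in live-birth rate, the as-treated difference is off by about 1 to 2 points in either direction against the 7-point margin. Balanced switching with equal prognosis gives none. The primary intention-to-treat conclusion stands regardless. This should be corrected, but it does not threaten the trial's main finding.

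**What to change.** In Section 9.5 and its copy at the front of the protocol:

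1. Call the comparison by treatment received as-treated, report it as descriptive only, and give switch counts and reasons by arm.
2. As the adherence sensitivity analysis, add a complier-average risk difference: the intention-to-treat difference divided by the between-arm difference in PGS uptake, with every woman in her randomised arm. State its assumptions: assignment affects live birth only through receipt of PGS (exclusion restriction), and nobody would do the opposite of her assignment whichever arm she drew (no defiers). Read its interval, at the same confidence level as the primary analysis, against the 7-point margin.
3. If a per-protocol set is also kept, exclude switchers from both arms by one rule, never move them across, and state that it is not a fully randomised comparison. It should not be the main remedy, because about half the bias remained in the one-way example.

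The cost is SAP wording. Section 5.1.4 already has switching tracked, so no new data are needed beyond reporting reasons by arm. The complier-average interval is about 5% wider than the intention-to-treat interval at 5% switching. With so little switching the two estimates will be close, so its main value is that it keeps the randomised arms.

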The tertiary outcomes such as the rates of pregnancy, pregnancy loss and live birth after the first transfer will be analyzed with Pearson chi-square test. Cost-effectiveness analysis will be done by decision analytic model with TreeAge Pro 2014 (2014 Version; TreeAge software). Cost effectiveness is defined as an incremental cost effectiveness ratio (ICER). The ICER for live birth was calculated as the difference in cost between two treatment groups divided by the difference in live birth rates between the two groups. The secondary analysis will be performed according to per-protocol analyses. The primary and secondary outcomes will be compared according to actual treatment that subjects received and among subjects who complete embryo transfer(s).

Subgroup analyses will be performed according to different stimulation protocol (e.g. agonist long, agonist short, and antagonist protocol), different endometrial preparation protocol for FET (e.g. natural ovulation cycle and artificial cycle), age groups (e.g. 20~30 group, 30~35 group and >35 group), with or without history of recurrent spontaneous abortion.

Any deviations from the previously described statistical plan will be described and justified in a protocol amendment.

03/07/17

**Cumulative live birth rate with eSET after in-vitro fertilization with preimplantation genetic screening by next-generation sequencing versus conventional in-vitro fertilization: A pragmatic randomized controlled clinical trial (CESE-PGS)**

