### **Sample Size and Population**

03/07/2017

We aim to enroll good-prognosis women who are undergoing their first cycle of IVF. The targeted population is women age 20 to 37y, with 3 or more good-quality blastocysts obtained on day 5 of embryo culture. The exclusion criteria are women with a uterine cavity abnormality or women who plan to undergo preimplantation genetic diagnosis (PGD). Given the likelihood of a high proportion of mosaic embryos in the PGS group and our decision to not transfer mosaic embryos (which are unlikely to achieve live birth and have an unknown risk-benefit ratio), we assume that the cumulative live birth rate after the transfer of PGS-selected euploid blastocysts will unlikely exceed that after serially transferring all the 3 untested blastocysts. This study is therefore designed as a non-superiority study. It is estimated the cumulative live birth rate after 3 single embryo transfers is 65% in each group. To be 80% certain that the upper limit of a one-sided 95% confidence interval (CI) would exclude a difference in favor of the PGS group by more than 7%, 575 patients are required in each group. In consideration of 5% drop-out rate, a total of 1208 subjects will be enrolled. The randomization will be stratified by study site. Blocked randomization will be used with dynamic block size. The random number sequence will be generated by the data coordinating center and will be unknown to all investigators. The randomization will be performed on day 5 of embryo culture via a central online randomization system. At present, 8 centers have volunteered and qualified to participate in subjects' enrollment. It is planned that each center will approximately enroll 80 subjects.

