## 9.3 Sample Size and Accrual

Given the possibility of false positive and the decision of not transferring mosaic embryos which are probably to develop into live birth, we assume that the cumulative live birth rate after transferring PGS-selected euploid embryos will be similar with that after serially transferring all the 3 untested blastocysts. This study is designed as a non-superiority study. It is estimated the cumulative live birth rate after 3 single embryo transfers is 65% in the IVF control group. We set a non-superiority margin at an absolute difference of 7% to retain approximately 90% of the clinical effect of the control group. To be 80% certain that the upper limit of a one-sided 95% confidence interval (CI) of absolute difference between groups to reject null hypothesis that PGS is superior to conventional IVF, 575 pa-

tients were required in each group. In consideration of 5% drop-out rate, a total of 1208 subjects will be enrolled. At present, 8 centers have volunteered and qualified to participate in subjects' enrollment. It is planned that each center will approximately enroll 150 subjects.

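### Subgroup analyses have no interaction test and no exploratory label, and one of the two factors kept in the final analysis (endometrial preparation) is fixed only after randomisation

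*Combined protocol and SAP*

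**What the plan says.** The subgroup plan is one sentence in section 9.5, repeated in the statistical text at the front of the document. It begins "Subgroup analyses will be performed according to different stimulation protocol (e.g. agonist long, agonist short, and antagonist protocol" and adds endometrial preparation (natural or artificial cycle), three age bands, and women "with or without history of recurrent spontaneous abortion". Most levels are given only as examples, so the strata are not closed, and a woman aged 30 fits two of the age bands. The sentence names no outcome, test, interaction term, multiplicity rule or exploratory status.

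The Final statistical analysis is shorter: "Subgroup analyses were performed according to different endometrial preparation protocol for frozen embryo transfer and age groups". It sets a general two-sided P<0.05 and restricts the non-superiority test to the primary hypothesis. It too has no interaction test and no exploratory label. Stimulation protocol and recurrent-abortion history are absent.

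The paragraph that closes section 9.5 promises that deviations will be described and justified in a protocol amendment. The front page says there was only one protocol version, and the Summary of changes lists only the move from a 95% to a 90% CI.

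**The concern.** A significant result in one stratum and a non-significant one in the next does not show that the effect differs between them; only an interaction test addresses that. Without one, and without an exploratory label, the natural product of this plan is a list of stratum comparisons judged at 0.05, some of which will be positive by chance.

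This matters for age in particular. The background (section 2.2) gives a separate result for women aged 35 to 40 in one trial and an age contrast in an observational study, so a chance finding in an age stratum could be taken as identifying who benefits.

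Endometrial preparation has a further problem. Under section 5.3.1 the site investigator chooses it after oocyte retrieval, hence after the day-5 randomisation, and section 5.2 says the trial is unblinded. Under section 6.2.3, PGS women with no euploid embryo leave the intervention, so they need not have any preparation. Strata defined this way do not hold the randomised groups intact.

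**Working it through.** **1. The plan's own figure.** Section 9.3 supplies three inputs. The control rate: "It is estimated the cumulative live birth rate after 3 single embryo transfers is 65% in the IVF control group". The margin, which is 7 percentage points on the absolute scale. The level and power: "To be 80% certain that the upper limit of a one-sided 95% confidence interval (CI") clears that margin. With the same 65% in both arms:

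n per arm = (1.645 + 0.842)² × 2 × 0.65 × 0.35 / 0.07² = 574.1, rounded up to 575.

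This matches the synopsis: "575 patients are required in each group". Adding 5% gives 575 × 1.05 = 603.75, so 604 per arm and 1208 in all. The inputs are therefore read as intended.

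**2. Number of strata.** Section 9.5: 3 (stimulation) + 2 (preparation) + 3 (age) + 2 (recurrent abortion) = 10. Final analysis: 2 + 3 = 5, if the section 9.5 age bands were used.

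**3. Ceiling if strata were independent.** 1 − 0.95^10 = 0.40; 1 − 0.95^5 = 0.23. These are too high, because the same women are counted once under each factor.

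**4. Allowing for the overlap.** Simulated trials with 604 per arm, 65% live birth in both arms, factors independent of each other, and each stratum tested at two-sided 0.05. The documents give no stratum shares, so several sets were assumed: from equal shares to, for example, age 50/35/15%, stimulation 60/20/20%, preparation 50/50% and recurrent abortion 5/95%.

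| Strata | Any significant stratum | Any significant in favour of PGS |
|---|---|---|
| 10 (section 9.5) | 0.32 to 0.34 | 0.17 to 0.18 |
| 5 (final analysis) | 0.20 to 0.21 | 0.10 to 0.11 |

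The results hardly move with the shares. They are for one outcome.

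**5. Endometrial preparation.** Section 2.1 gives about 60% euploidy and three blastocysts are tested. Assuming embryos are independent, P(no euploid) = 0.4³ = 0.064, or about 0.064 × 604 = 39 women in the PGS arm. Section 9.2.1 counts them in the denominator as women without a live birth. If a preparation subgroup holds only women who had a preparation, they drop out of the PGS arm alone. As an illustration, suppose both arms truly have 65% and all IVF women receive a preparation: the PGS rate among women with a preparation becomes 0.65 / 0.936 = 69.4%, an apparent gain of 4.4 points with no true overall difference. The simulation in step 4 treats preparation as a complete baseline factor, so it does not include this bias.

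**6. The alternative.** One interaction test for each of the three pre-randomisation factors, treated as independent, gives 1 − 0.95³ = 0.14.

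**The case against.** Section 9.5 names no test for subgroups, and it analyses the primary outcome by a risk difference and confidence interval, so testing within strata at 0.05 is a reading of the plan. That stands for section 9.5. In the final text the general P<0.05 sentence has no exception for subgroups, which makes the reading reasonable there.

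The plan also ranks its outcomes as primary, secondary and tertiary, states no subgroup hypothesis, and attaches no success criterion to a subgroup. That lowers the stakes: the primary conclusion is untouched. The background's contrast at age 37 cannot arise here either, since enrolment stops at 37. None of this supplies the missing interaction test or label.

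Three stronger readings are tempting and are not supported.

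- A reader might infer that the 7-point rule will be applied within age strata and will nearly always fail in at least one. With zero true difference and a one-sided 5% level, the chance of at least one failure is indeed 0.92 or more for every age split tried. But section 9.5 states the rule for the overall comparison of PGS with IVF ("if the upper limit of the 95% CI of absolute risk difference was shown to lie below the non-superiority margin of 7"%), and the final text confines the test to the primary hypothesis. The figure also falls to 49 to 62% if PGS is assumed to be 5 points lower. It describes low power in small strata, not an error rate of a planned analysis.
- A reader might take one in three as the rate for the final analysis. It belongs to the four-factor plan; for the two factors kept it is about one in five.
- A reader might infer that two factors were dropped because of their results. The documents give no reason at all.

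**Conclusion.** The concern holds. Both texts plan subgroup analyses without an interaction test or exploratory label. With no true effect and stratum comparisons at two-sided 0.05, the chance of at least one false significant stratum is about 20% for the final two factors and about 33% for the four in section 9.5; the share favouring PGS is roughly half of each. These figures rest on assumed stratum shares, 65% in both arms, one outcome, and the section 9.5 levels being the ones used.

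The endometrial-preparation subgroup is not a randomised comparison, whatever the test. About 6% of the PGS arm may have no preparation, given 60% euploidy and independent embryos.

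The move from four factors to two is a departure that section 9.5 says should be described and justified, and the Summary of changes does not mention it. The primary analysis is unaffected. The point should be corrected because the published subgroup results could mislead.

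**What to change.** In section 9.5 and the Final statistical analysis:

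- For cumulative live birth, give one treatment-by-factor interaction test for each pre-randomisation factor: age, stimulation protocol, recurrent-abortion history.
- List the strata in full and make the age bands non-overlapping.
- Show stratum risk differences with 95% CIs and no stratum P values, and label all subgroup results exploratory.
- Report endometrial preparation descriptively, as a post-randomisation factor, with the number of women in each arm who have no preparation.
- Report all planned baseline factors, or state in the Summary of changes why any was dropped.

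This is wording and a few model terms on data already collected. The cost is low power. For a factor split in half, the interaction has standard error √(2 × 2 × 0.65 × 0.35 / 302) = 0.055, so 80% power at two-sided 0.05 needs effects that differ by about (1.96 + 0.842) × 0.055 = 15 percentage points. A non-significant interaction therefore would not show that the effect is uniform, and the report should say so.
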